#### Vaccinations:

Sirolimus may affect the response to vaccinations. Sirolimus should be paused 14 days before until 14 days after receiving a live vaccine. The SmPC of sirolimus recommends avoiding live vaccinations during therapy. Individual risk/ benefits should be discussed with infectious disease specialists.

#### Surgical interventions:

Treatment with sirolimus may affect wound healing. We recommend pausing treatment 14 days before until 14 days after elective surgical interventions. For non-elective interventions, therapy should also be paused until 14 days after the procedure.

Table 6: Sirolimus dose modifications for toxicities

This section is adapted from [23].

|                                                                                                                                                                       |                                                                                                                                                                                                                                                                                                                                                                                                                       |
|-----------------------------------------------------------------------------------------------------------------------------------------------------------------------|-----------------------------------------------------------------------------------------------------------------------------------------------------------------------------------------------------------------------------------------------------------------------------------------------------------------------------------------------------------------------------------------------------------------------|
| Non-infectious pneumonitis grade 2                                                                                                                                    | Interrupt study drug administration until resolution to $\leq$ grade 1. If resolution occurs within $\leq 4$ weeks, study drug should be re-started at the dose level prior to interruption. If resolution takes $> 4$ weeks, or if event recurs, hold study drug until recovery to $\leq$ grade 1 and reduce subsequent doses to 50%.                                                                                |
| Non-infectious pneumonitis grade 3                                                                                                                                    | Interrupt study drug administration until resolution to $\leq$ grade 1. If resolution occurs $\leq 4$ weeks reduce subsequent doses to 50%. If resolution takes $> 4$ weeks, discontinue study drug.                                                                                                                                                                                                                  |
| Non-infectious pneumonitis grade 4                                                                                                                                    | Discontinue study drug                                                                                                                                                                                                                                                                                                                                                                                                |
| Intolerable grade 2 and 3 mucositis                                                                                                                                   | Interrupt study drug administration until resolution to $\leq$ grade 1. If resolution occurs within $\leq 7$ days, study drug should be re-started at the dose level prior to interruption. If resolution takes $> 7$ days, or if event recurs within 28 days, hold study drug until recovery to $\leq$ grade 1 and reduce subsequent doses to 50%.                                                                   |
| AST or ALT elevation grade 1 ( $> \text{ULN} - 3.0 \times \text{ULN}$ ) or grade 2 ( $> 3.0 - 5.0 \times \text{ULN}$ )                                                | Maintain current dose level                                                                                                                                                                                                                                                                                                                                                                                           |
| AST or ALT elevation grade 3 ( $> 5.0 - 20.0 \times \text{ULN}$ )                                                                                                     | Interrupt study drug administration until resolution to $\leq$ grade 1 (or $\leq$ grade 2 if screening values were within the range of grade 2). If resolution occurs $\leq 7$ days, study drug should be re-started at the dose level prior to interruption. If resolution takes $> 7$ days, or if event recurs within 28 days, hold study drug until recovery to $\leq$ grade 1 and reduce subsequent doses to 50%. |
| AST or ALT elevation grade 4 ( $> 20 \times \text{ULN}$ )
Recurrence of grade 4 after dose reduction or toxicity requiring study drug interruption for $> 28$ days | Interrupt study drug administration until resolution to $\leq$ grade 1 (or $\leq$ grade 2 if screening values were within the range of grade 2). If resolution occurs $\leq 7$ days reduce subsequent doses to 50%. If resolution takes $> 7$ days, discontinue study drug.                                                                                                                                           |
| Any other grade 4                                                                                                                                                     | Hold study drug until recovery to $\leq$ grade 1 or screening value. Reduce subsequent doses to 50%.                                                                                                                                                                                                                                                                                                                  |
| Recurrence of grade 4 after dose reduction                                                                                                                            | Discontinue study drug                                                                                                                                                                                                                                                                                                                                                                                                |
| Grade 3 or 4 clinical liver failure (asterixis or encephalopathy/coma)                                                                                                | Discontinue study drug                                                                                                                                                                                                                                                                                                                                                                                                |
| Any non-hematologic toxicity requiring study drug interruption for $> 28$ days                                                                                        | Discontinue study drug                                                                                                                                                                                                                                                                                                                                                                                                |
| Grade 2 thrombocytopenia                                                                                                                                              | No action                                                                                                                                                                                                                                                                                                                                                                                                             |
| Grade 3 thrombocytopenia                                                                                                                                              | Interrupt study drug until resolution to $\leq$ grade 1 or screening level. If resolution occurs $\leq 7$ days, reintroduce study drug at the dose level prior to interruption. If resolution occurs $> 7$ days, or event reoccurs within 28 days, reduce subsequent doses to 50%.                                                                                                                                    |
| Grade 4 thrombocytopenia                                                                                                                                              | Interrupt study drug until recovery to $\leq$ grade 1. Then reduce subsequent doses to 50%.                                                                                                                                                                                                                                                                                                                           |
| Grade 2 neutropenia or anaemia                                                                                                                                        | No action                                                                                                                                                                                                                                                                                                                                                                                                             |
| Grade 3 neutropenia or anaemia                                                                                                                                        | Interrupt study drug until resolution to $\leq$ grade 1 or screening level. If resolution occurs $\leq 7$ days, reintroduce study drug at the dose level prior to interruption. If resolution occurs $> 7$ days, or event reoccurs within 28 days, reduce subsequent doses to 50%.                                                                                                                                    |
| Grade 4 neutropenia or anaemia                                                                                                                                        | Interrupt study drug until recovery to $\leq$ grade 1. Then reduce subsequent doses to 50%.                                                                                                                                                                                                                                                                                                                           |
| Febrile neutropenia                                                                                                                                                   | Interrupt study drug until resolution to $\leq$ grade 1 or screening level. If resolution occurs $\leq 7$ days, reintroduce study drug at the dose level prior to interruption. If                                                                                                                                                                                                                                    |

|                                                                    |                                              |                                |
|--------------------------------------------------------------------|----------------------------------------------|--------------------------------|
| Clinical Trial Code: PROTECT
EU trial number: 2022-502332-39-00 | Trial Protocol
(Version 06; (01.10.2024)) | Page 62 of 110
CONFIDENTIAL |
|--------------------------------------------------------------------|----------------------------------------------|--------------------------------|

|                                                                          |                                                                                               |
|--------------------------------------------------------------------------|-----------------------------------------------------------------------------------------------|
|                                                                          | resolution occurs > 7 days, or event reoccurs within 28 days, reduce subsequent doses to 50%. |
| Any hematologic toxicity requiring study drug interruption for > 28 days | Discontinue study drug                                                                        |

Re-initiation of treatment with the IMP will be done under close and appropriate clinical and/or laboratory monitoring if according to the investigator's medical judgment the concerned event is unlikely to be related to the IMP and if the selection criteria for the trial are still met. For all temporary treatment discontinuations, duration must be recorded by the investigator in the appropriate pages of the eCRF.

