##### **5.5.4.3 Management of stomatitis / oral mucositis / mouth ulcers**

Caregivers should be instructed to report the first onset of buccal mucosa irritation/reddening to their study team immediately.

Stomatitis/oral mucositis/mouth ulcers due to the study drug should be treated using local supportive care. Interruption or discontinuation of sirolimus should be considered (see section 5.5.3, Table 6, section 7).

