##### **5.5.4.5 Management of non-infectious pneumonitis**

Non-infectious pneumonitis is a class effect of rapamycin derivatives. Cases of interstitial lung disease (including pneumonitis, and infrequently bronchiolitis obliterans with organizing

|                                                                    |                                              |                                |
|--------------------------------------------------------------------|----------------------------------------------|--------------------------------|
| Clinical Trial Code: PROTECT
EU trial number: 2022-502332-39-00 | Trial Protocol
(Version 06; (01.10.2024)) | Page 63 of 110
CONFIDENTIAL |
|--------------------------------------------------------------------|----------------------------------------------|--------------------------------|

pneumonia [BOOP] and pulmonary fibrosis), with no identified infectious etiology have occurred in adult patients receiving immunosuppressive regimens including sirolimus. Some of these have been severe and on rare occasions, a fatal outcome was observed. In some cases, the interstitial lung disease has resolved upon discontinuation or dose reduction of sirolimus. These risks may increase with higher sirolimus trough levels. Individuals participating in this trial will be routinely assessed for the occurrence of new or changes in existing pulmonary symptoms consistent with lung toxicity. Consultation with a pulmonologist is recommended for any case of pneumonitis that develops during the study.

A diagnosis of non-infectious pneumonitis should be considered in patients presenting with non-specific respiratory signs and symptoms such as hypoxia, pleural effusion, cough, or dyspnea, and in whom infectious, neoplastic and other non-medicinal causes have been excluded by means of appropriate investigations. Caregivers should be advised to promptly report any new or worsening respiratory symptoms.

Consider corticosteroids if infective origin is ruled out. Taper as medically indicated.

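### Section 5.5.3 gives conflicting rules for restarting sirolimus after toxicity: Table 6 against the paragraph below it, and two Table 6 rows once grade 2 pneumonitis interrupts treatment for more than 28 days

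*Protocol*

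**What the plan says.** All of the operative text is in Protocol section 5.5.3, with supporting text in 5.5.4.

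- **Table 6** sets sirolimus dose changes for toxicity. Most rows are triggered by event type and grade, and none carries a causality condition. Several restart the drug at the prior dose if the event resolves in time. Others resume at half dose; the row for any other grade 4 event, for example, holds the drug until recovery to grade 1 or the "screening value. Reduce subsequent doses to 50" percent.
- **The paragraph after Table 6** says that re-initiation will be done under close monitoring if, in the investigator's medical judgement, "the concerned event is unlikely to be related to the IMP and if the selection criteria for the trial are still met".
- **Grade 2 non-infectious pneumonitis:** restart at the prior dose if resolved within 4 weeks. Otherwise: "If resolution takes $> 4$ weeks, or if event recurs, hold study drug until recovery to" grade 1 or lower, then continue at 50%.
- **Grade 3 non-infectious pneumonitis:** restart at 50% if resolved within 4 weeks. Otherwise: "If resolution takes $> 4$ weeks, discontinue study drug".
- **A later row:** "Any non-hematologic toxicity requiring study drug interruption for $> 28$ days" leads to discontinuation.

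Section 5.5.4.3 states "Stomatitis/oral mucositis/mouth ulcers due to the study drug should be treated using local supportive care" and points to Table 6 for interruption. Section 5.5.4.5 states "Non-infectious pneumonitis is a class effect of rapamycin derivatives" and considers the diagnosis in patients "in whom infectious, neoplastic and other non-medicinal causes have been excluded by means of appropriate investigations".

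**The concern.** These are operative dosing instructions for infants, on a product not authorised under 18 years. If table and paragraph disagree for a drug-related event, one site can restart sirolimus and another withhold it, each following the text. Either outcome may be the wrong one: re-exposure after a related toxicity, or loss of treatment that the table meant to continue. A child taken off early might also miss the 9 months of treatment that section 9.1 requires for the per-protocol set.

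The existing safeguards do not say which rule prevails. Section 5.5.5 requires discussion with the sponsor for interruptions of 7 days or more, which helps, but a shorter interruption followed by a restart is not caught. Second assessment (8.8.1), DSMB review (12.5.1) and the individual risk-benefit evaluations (1.3.10) give no order of precedence either.

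**Working it through.** The protocol gives no figure to reproduce here. The check compares rules and then estimates how many children could be concerned.

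**Step 1. Count the Table 6 rows.** As extracted there are 19.

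| Action | Rows | Count |
|---|---|---|
| Restart at prior dose if resolved in time | pneumonitis G2 (4 weeks); mucositis G2-3, AST/ALT G3, thrombocytopenia G3, neutropenia/anaemia G3, febrile neutropenia (each 7 days) | 6 |
| Resume only at 50% | pneumonitis G3 (within 4 weeks), AST/ALT G4 (within 7 days), any other G4, thrombocytopenia G4, neutropenia/anaemia G4 | 5 |
| Discontinue only | pneumonitis G4, recurrent G4, liver failure G3-4, two rows for interruption over 28 days | 5 |
| No change | AST/ALT G1-2, thrombocytopenia G2, neutropenia/anaemia G2 | 3 |

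Restart rows: 6 + 5 = 11 of 19. The AST/ALT grade 4 row may be two rows merged by the PDF reading; leaving it out gives 10 of 18.

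**Step 2. Table against paragraph.** Take a grade 3 neutropenia that resolves on day 6 and is judged related. By the table, 6 ≤ 7 days, so sirolimus is reintroduced at the prior dose. By the paragraph, the event is not unlikely to be related, so the condition fails. Because 6 < 7, section 5.5.5 does not require discussion with the sponsor. Table 6 clearly has related events in view, at least in part: 5.5.4.3 sends drug-caused stomatitis to it, and 5.5.4.5 describes pneumonitis as a class effect considered after other non-medicinal causes are excluded.

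**Step 3. The selection criteria.** Inclusion criterion 2 requires treatment initiation before 4 months of age. Exclusion criterion 2 bars past systemic mTOR inhibitor use. If these had to be met again at restart, every child who has taken sirolimus would fail the second, and any child aged 4 months or more would fail the age limit.

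**Step 4. Pneumonitis row against the 28-day row.** 4 weeks × 7 = 28 days, but the rows measure different things: time to resolution in one, length of interruption in the other.

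- Illustration A: drug held for 35 days until resolution. 35 > 28 on both measures, so one row says resume at 50% and the other says discontinue.
- Illustration B: onset day 0, drug held from day 5, resolved day 31. If resolution time counts from onset, it is 31 days (> 28), so the 50% branch applies. The interruption is 31 − 5 = 26 days (< 28), so the stop row is not triggered and there is no conflict.

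The conflict therefore exists only when the interruption itself exceeds 28 days. There the grade 3 row discontinues, so the milder grade has the looser rule.

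**Step 5. How many children.** Section 1.3.7.1 summarises three cohorts of children treated before age 2, of 17, 45 and 21.

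- In the cohort of 45, 7 children had a grade 3 event. At most 2 of the itemised events (stomatitis, abnormal blood count) fit a restart row: 2/45 = 4.4%, exact 95% CI 0.5% to 15.1%. Times 30 treated children: 1.3 (0.2 to 4.5).
- The cohort of 17 had no grade 3-4 event. Pooled: 2/(45 + 17) = 2/62 = 3.2%; × 30 = 1.0.
- Grade 4: 0/(17 + 45 + 21) = 0/83. One-sided 95% upper limit 1 − 0.05^(1/83) = 3.5%; × 30 = 1.1.

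**The case against.** **The paragraph says *if*, not *only if*.** A reader might infer an outright ban on restarting after any related event. The text does not say that. It could be read cumulatively, with the table giving timing and dose and the paragraph adding monitoring and a further condition. What stands against this is that a stated condition has no purpose if the drug is restarted when it is not met, and that the table's rows carry no such condition.

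**Eleven rows are not eleven conflicts.** Section 5.5.4.1 also sends infections to Table 6, and raised transaminases or neutropenia can have causes other than sirolimus. Where the event is judged unlikely to be related, table and paragraph agree on causality. The count shows where a conflict can arise. Nor is the causality scale in 8.4.2, which counts an event as related when a link cannot be excluded, invoked by the paragraph; that relies on medical judgement.

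**Sponsor discussion.** Every pneumonitis interruption over 28 days will already have reached the sponsor under 5.5.5, so differing decisions between sites are unlikely for that part. This stands. It does not cover restarts after interruptions shorter than 7 days, which are possible under the five prior-dose rows with a 7-day limit.

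**The selection criteria.** They are framed around enrolment, and the authors surely meant the ones that can change. That is likely, but the paragraph does not say so.

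**Specific over general.** The grade 2 pneumonitis row could be an intended exception. The 28-day row, however, covers any non-hematologic toxicity and names no exception.

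**Conclusion.** Two conflicts stand: table against paragraph for events judged related, and the grade 2 pneumonitis branch against the 28-day row once the interruption exceeds 28 days. The second is direct; the first rests on the natural reading of a conditional sentence. The literal impossibility of meeting the selection criteria again adds to the first.

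This should be fixed, but it does not threaten the trial. About 1 of 30 treated children might reach a restart row. That assumes the cited rates carry over, the cohorts do not overlap, the stomatitis was intolerable and the blood-count abnormality fits a restart row. The cohort of 21 reports no grade 3 count and targeted troughs of 3-4 ng/ml against 5-10 ng/ml here. The share of events judged related and the frequency of prolonged grade 2 pneumonitis are not given, so the number of children facing an actual conflict is unknown. The primary analysis follows the treatment policy strategy (9.4) and is unaffected.

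A reader might also infer, from 7.2 read with the rule in 8.2 that every serious adverse reaction is unexpected, that a first related serious event ends treatment, against 7.1 and several Table 6 rows. The documents do not establish this. If the word for recurrence in 7.2 governs both items, or if 8.2 serves safety reporting only, nothing conflicts.

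**What to change.** In section 5.5.3:

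1. **Grade 2 pneumonitis row.** Discontinue when the interruption exceeds 28 days, keeping the 50% restart for recurrence or shorter interruptions. Alternatively, mark the branch as an explicit exception to the 28-day row.
2. **Re-initiation paragraph.** State either that it applies only to events Table 6 does not cover, with Table 6 governing the toxicities it lists, or that it overrides Table 6 for related events. The sponsor's medical team should choose.
3. **Selection criteria.** Replace the general reference with the specific safety criteria to be rechecked at restart, such as contraindication and laboratory values.

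Optionally, clarify in 7.2 whether a first related serious event ends treatment; this is wording advice, not correction of an error.

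The cost is an amendment of existing sentences with the approvals required by 12.3, plus notice to sites. No new data and no change to the analysis are needed. Last subject last visit is planned for Q2 2029 (3.2), so the correction can still serve children on treatment.
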